### Ethics Approval

This study will be performed in accordance with the Declaration of Helsinki. Ethics approval has been granted by the Research Ethics Committee of the Hospital das Clínicas da Faculdade de Medicina da Universidade de São Paulo (#51929221.7.0000.0068). 

### Consent to Participate

Written informed consent will be obtained by researchers from all study participants.

### Analysis of the Population

Exclusion criteria will include participation in another research study, difficulty understanding any questionnaires, and pregnancy or psychiatric problems that make it difficult to understand the questionnaires and study protocol. If a patient misses any session, they will be contacted by telephone to confirm the reason, and the session will be rescheduled. Attending a total of 6 sessions will be considered the cut-off point to establish patient compliance [18-20]. An intention-to-treat analysis will be performed using the patient’s most recent assessment in the case of withdrawal from the study or the absence of data. The intervention will be conducted by a trained physiotherapist who is not otherwise directly involved in the assessments. In case of possible injuries occurring during the intervention period, the individuals will be referred for appropriate treatment.

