## Methods

### Study Design

This prospective cohort study will be conducted at a university hospital that provides specialized asthma treatment. The study protocol was developed following the SPIRIT (Standard Protocol Items: Recommendations for Interventional Trials) checklist guidelines [14], and the trial was registered at ClinicalTrials.gov (NCT05159076). The study design is illustrated in Figure 1. Individuals with asthma will be enrolled in the trial after a routine medical consultation. Baseline lung function will be checked from the medical records. Eligible participants will undergo an 8-week behavioral intervention protocol to increase PADL and reduce sedentary behavior. First, all included individuals will receive an educational program, followed by an intervention aimed at increasing physical activity. All individuals will be assessed before and after the 8-week intervention and then 16 weeks later. The outcomes assessed will include anthropometric variables, clinical asthma control, health-related quality of life, physical activity levels, anxiety and depression symptoms, exacerbations, body composition, barriers to performing PADL, and physical activity behavioral stages (Figure 1).

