#### Primary Outcome: PADL

PADL will be objectively assessed using an activity monitor (ActiGraph GT9X), a device that monitors frequency, intensity, and duration [27] in real time and is considered a sensitive and reliable method [28,29]. This triaxial monitor provides measurements of the amount and intensity of PADL and the monitoring of posture [27,30] through variations in acceleration. The “counts” obtained in a given period of time are linearly related to the intensity of the patient’s physical activity in this period [29]. Individuals will be instructed to use the accelerometer, attached to the hip using an elastic belt, for 7 consecutive days. All accelerometers will be initialized to collect data in 60 “epochs” on the 3 axes using ActiLife (version 6.9.5; ActiGraph) software. The following data will be later analyzed using the same software: the number of daily steps and the time spent in sedentary, light, moderate, and vigorous states of activity. Moderate to vigorous physical activity will also be evaluated. Sedentary behavior will be assessed using the same activity monitor.

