### Sample Size Calculation

A minimum number of 17 individuals in at least one of the groups (responder or nonresponder) was established to detect a difference of 2500 (SD 2500) steps [45] in the primary outcome (α=5%, 1 – β=80%). A sample of 100 participants was established, considering the percentage of nonresponders (17%) as previously observed [5]. Clinical improvement in the ACQ score (≥0.5) [3,32] will be considered a secondary outcome.

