### Statistical Analysis Planning

Individuals will be stratified as “responders” and “nonresponders” based on an increase of ≥2500 steps [45]. The Kolmogorov-Smirnov test will be used to assess data normality. Cluster analysis will be used to characterize the groups according to individual characteristics. Cluster analysis will be carried out in 2 stages: hierarchical analysis using the Ward method to determine the number of clusters and k-means analysis to group the clusters [46]. Comparisons of clinical, anthropometric, and psychosocial data obtained in the responder and nonresponder groups will be conducted using the 2-tailed *t* test or Mann-Whitney *U* test for continuous variables and the chi-square test for categorical variables. To determine the independent factors associated with the level of PADL (dependent variable, considering clinical control, smoking, obesity, anxiety, and depression as independent variables), multiple linear regression analysis (stepwise forward) will be used. The intra- and between-group comparison at baseline, short term, and medium term will be assessed using the 2-way ANOVA with repeated measures test. The significance level will be adjusted to 5% (*P*<.05) for all tests. If necessary, intention-to-treat analysis will be performed, as described earlier. SPSS Statistics (version 22.0; IBM Corp) will be used for statistical analysis. Data integrity will be monitored by regularly scrutinizing data files for omissions and errors. Participants will be given an anonymous study ID to protect confidentiality, and only study investigators will have access to the final trial data set.

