### Strengths and Limitations of the Study

In addition to the potential to identify the characteristics of responders and nonresponders, this study will also follow up 4 months after training, considered the medium term. These results will allow us to determine if behavioral changes are maintained in the responders over time. The assessment of PADL using accelerometers as a primary outcome is a study strength because it is an objective outcome measure, thus decreasing the risk of bias. The fact that the study will be performed in only 1 hospital center can be considered a limitation.

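### Carrying the last assessment forward labels patients without week-8 accelerometry as nonresponders and credits week-8 responders lost to follow-up with their full gain

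*Protocol article*

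**What the plan says.** Under Analysis of the Population, the protocol article plans an intention-to-treat analysis that uses the patient's "most recent assessment in the case of withdrawal from the study or the absence of data". Statistical Analysis Planning refers back to this rule: "If necessary, intention-to-treat analysis will be performed, as described earlier". No other handling of missing data is stated.

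The visits are few: "All individuals will be assessed before and after the 8-week intervention and then 16 weeks later". Table 2 (Participant Timeline) shows physical activity measured at enrolment, at 8 weeks and at the 16-week follow-up. The outcome device is the ActiGraph (Primary Outcome: PADL). The smartwatch worn during the programme serves the weekly counselling sessions (Interventions).

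Patients are split into responders and nonresponders "based on an increase of ≥2500 steps". Changes over time are compared with a "2-way ANOVA with repeated measures test". Of the follow-up, Strengths and Limitations of the Study says: "These results will allow us to determine if behavioral changes are maintained in the responders over time".

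**The concern.** In most trials a carry-forward rule affects the value of an endpoint. Here it also decides who belongs to which group, and describing those groups is the first objective. A patient with no week-8 accelerometry has only the enrolment value to carry, so the computed change is 0 whatever the patient actually did. The nonresponder group then holds two kinds of patient: those measured and found not to have gained 2500 steps, and those never measured. Any characteristic linked to leaving the study could be reported as a characteristic of nonresponse. The planned nonresponder group is small (17 of 100), so a few such patients change its make-up.

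The second objective is affected differently. A responder at week 8 who misses the later visit is given the week-8 value again. For that patient maintenance is assumed, although maintenance is what the follow-up is meant to measure.

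**Working it through.** **Inputs from the protocol article.** Difference and SD: "detect a difference of 2500 (SD 2500) steps"; alpha 5%, power 80%, 17 in the smaller group, 17% nonresponders, 100 enrolled (Sample Size Calculation). Threshold 2500 steps (Statistical Analysis Planning).

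**Assumed inputs.** Loss before week 8, *d*: 5%, 10%, 20%. Share of week-8 responders lost afterwards, *f*: 10% to 30%. True nonresponse, *q*: 17% or 50%. Both kinds of loss are taken as unrelated to true response or retention.

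**1. The plan's own figures.** By the normal formula, n per group = 2 × (1.96 + 0.84)² × (2500/2500)² ≈ 15.7, so 16. The exact two-sided t test gives 16.7, so 17. The total is 17 / 0.17 = 100. Both stated figures reproduce, and neither contains an allowance for dropout.

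**2. The label.** For a patient without week-8 accelerometry, carried change = baseline − baseline = 0, which is below 2500, so the label is nonresponder. The sentence defining response does not name the visit. If the label were taken at the later follow-up, a patient who left before week 8 would still have a change of 0.

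**3. Make-up of the nonresponder group.** Labelled nonresponders = 100 × (1 − *d*) × *q* + 100 × *d*. With *q* = 17%:

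| Dropout *d* | Measured nonresponders | Dropouts | Labelled nonresponders | Dropouts' share |
|---|---|---|---|---|
| 5% | 16.2 | 5 | 21.2 | 24% |
| 10% | 15.3 | 10 | 25.3 | 40% |
| 20% | 13.6 | 20 | 33.6 | 60% |

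With *q* = 50%: at 10% dropout, 45 + 10 = 55, share 10/55 = 18%; at 20%, 40 + 20 = 60, share 20/60 = 33%.

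**4. Dilution of group differences.** With *q* = 17% and dropout unrelated to response, the labelled group contains all 17 true nonresponders, and the rest of it would have responded. A true 1-SD difference in a characteristic then shrinks to 17/21.2 = 0.80, 17/25.3 = 0.67 and 17/33.6 = 0.51 SD. With the labelled group sizes, the power of the two-sided t test is 90%, 82% and 66%, against 96% for 17 versus 83 with no dropout.

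**5. Maintenance in responders.** If a share *r* of the week-8 gain is truly kept, carry-forward shows *r* × (1 − *f*) + 1 × *f*. With *r* = 0.5:
- *f* = 10%: 0.45 + 0.10 = 55%
- *f* = 20%: 0.40 + 0.20 = 60%
- *f* = 30%: 0.35 + 0.30 = 65%

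If a 2500-step gain is wholly lost (*r* = 0), the analysis still shows 2500 × *f* = 250, 500 and 750 steps kept.

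**The case against.** The strongest reply is that the harm depends on a dropout rate the article does not give. Staff telephone patients who miss a session and reschedule it, the programme lasts only 8 weeks, and a missed session is not a missed week-8 assessment. This stands as a limit on size: with almost no missing accelerometry the effect is small.

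The 17% is also uncertain. The Introduction describes it as patients whose activity level did not improve, and does not tie it to a 2500-step threshold. If the true share is higher, dropouts weigh less, as the 50% figures show. This stands too.

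A third reply is that in a pragmatic study a patient who leaves may fairly count as a programme nonresponder. That is a defensible definition, and if dropouts are mostly true nonresponders the dilution in step 4 is smaller. But the article defines response by a gain in steps, and the carry-forward rule merges the two reasons for the label without showing them apart.

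Two stronger readings are tempting and are not supported:
- A reader might infer that every lost follow-up becomes a maintained gain. That is true only for patients with a measured week-8 gain. A week-8 nonresponder stays a nonresponder, and a patient with neither later measurement is carried at baseline, which can pull the average medium-term gain down.
- A reader might infer that the two sections contradict each other, because one states the intention-to-treat analysis outright and the other makes it conditional. The conditional sentence refers back to the first, whose rule applies only to withdrawal or absent data. The natural meaning is that it applies when data are missing.

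**Conclusion.** The concern holds for two groups: patients without week-8 accelerometry, and week-8 responders who miss the later visit. For the first, the nonresponder label follows from the rule and the visit schedule, whatever the reason for the missing value. For the second, maintenance is assumed, and is overstated if gains truly fade. If gains were fully kept there would be no such error. The article states the rule itself, so this is not a detail left to an analysis plan.

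The size is conditional. With 17% true nonresponse and dropout unrelated to response, dropouts make up 24% to 60% of the labelled nonresponders at 5% to 20% dropout. With 50% true nonresponse they make up 18% to 33% at 10% to 20% dropout. With half the gain truly kept and 10% to 30% of responders lost to follow-up, apparent retention is 55% to 65%. A reader might also infer that copied values make the standard errors too small. That has not been worked out for this design, and the conclusion does not rest on it.

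**What to change.** Remove carry-forward as the primary method in Analysis of the Population and in Statistical Analysis Planning, and put in its place:

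- **Outcomes over time.** For steps and the other continuous outcomes, a linear mixed model for repeated measures on all available visits from all enrolled patients, replacing repeated-measures ANOVA on filled-in values. SPSS offers this as MIXED.
- **Responder status.** Primary analysis by multiple imputation of week-8 steps, from baseline variables and any later step counts.
- **Patients without week-8 accelerometry.** A supportive table of their baseline characteristics, shown separately.
- **Sensitivity analysis.** Carry-forward, with missing counted as nonresponse, kept only under that label.
- **Wording.** Reword the conditional intention-to-treat sentence to say that the method applies if data are missing.

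The cost is revised wording and slightly more analysis work. No further measurements are needed. Recruitment was ongoing when the article appeared, so the change can be made before analysis if the data have not yet been analysed. The mixed model and the imputation rely on data being missing at random, which may fail; the sensitivity analysis probes this. Imputation does not replace lost measurements: at 10% dropout and 17% nonresponse, about 15.3 measured nonresponders are expected against the planned 17, and the report should state the number measured.

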### Procedures

#### Interventions

The intervention proposed here has been previously performed for individuals with asthma [5]. All individuals will participate in a brief asthma education program with 2 sessions, each lasting approximately 90 minutes. The educational program will be conducted in a class setting in the form of group discussions and video presentations. Educational topics will include asthma pathophysiology, medication and peak flow meter use, self-monitoring symptoms, environmental hygiene [1,21], and physical activity recommendations and benefits [15].

Behavioral interventions will be based on the transtheoretical model using counseling and incentives to increase the practice of physical activity [22,23]. Motivational interviewing, feedback, and guidelines for overcoming barriers will be used to stimulate individuals to reach their goals. Furthermore, individuals will receive a commercially available smartwatch activity monitor (Mi Band 5; Xiaomi) with an alarm that vibrates when the recommended daily number of steps is achieved and if the individual remains sedentary for 60 minutes. The main objective of the behavioral intervention will be to increase the level of PADL at any intensity, and the secondary objective will be to reduce sedentary time. The program will include 8 weekly face-to-face individual sessions, lasting up to 90 minutes each. At the beginning of the protocol, the motivational interview will identify the behavioral stage for physical activity practice using an appropriate questionnaire [24]. In addition, individuals will be asked to complete a daily physical activity diary and sign a contract with the health professional.

The data referring to the respective weeks of use will be reviewed for each behavioral intervention session. Each individual will receive advice based on their smartwatch data. Each session will address different topics related to physical activity practice and sedentary behavior, and individuals will be motivated and encouraged to make behavioral changes. In the last session, a motivational interview will be conducted to identify the individual’s behavioral stage, goals achieved, benefits gained, strategies used to overcome the most significant barriers, and proposed attitudes to keep themselves physically active in the long term. The schedule and content of each session are detailed in Table 1. The protocol of Freitas et al [25] will be modified by only changing the activity smartwatch monitor used during the intervention (Mi Band instead of Fitbit) [25].

**Table 1 table1:** Description of the behavioral change intervention sessions. Reproduced from Freitas et al [25] under CC-BY License [26] . In this study, Mi Band 5 replaces Fitbit Flex 2.

No. Week	Topics covered
Week 1: Lifestyle choices	Motivational interview to establish an educational diagnosis Identify the behaviour stage regarding physical activity Raise awareness of physical activity benefits Provide the Fitbit Flex 2 and ask them to wear it for at least 3 days each week
Week 2: Why become physically active?	Raise awareness of the physical activity international recommendations Deepen the knowledge about the physical activity benefits for patients with asthma Review Fitbit Flex 2 data of the past week and set one smart weekly goal (number of steps) Establish the action planning (goal) and sign a contract Evaluate the confidence of patients in achieving the goal (self-efficacy) Explain about the use of the workbook, diary and vibration alert
Week 3: Sedentary behaviour	Raise awareness of the risks of prolonged uninterrupted periods of sitting Ask them to start monitoring their sitting time (diary in a workbook) Discuss strategies to stand up/break up the sedentary time, according to the Fitbit Flex 2 vibration function Review achievement (using the diary and Fitbit Flex 2 data) of the current goal Discuss progress of the current goal Set one smart weekly goal (number of steps)
Week 4: Dealing with barriers	Dealing with barriers (as part of action and coping planning) Brainstorm the main barriers and possible solutions/modifications Discuss preferred activities Invite participants to come up with ideas for walking (progression in duration/intensity) Congratulate patients on any success (positive reinforcement) and ask them to reflect on any difficulties Review achievement (using the diary and Fitbit Flex 2 data) of the current goal Progress the current smart goal (number of steps and sedentary behaviour)
Week 5: Self-control	Facilitate self-control (how to self-monitor the negative and positive behaviours regarding PA) Identify the benefits acquired with the lifestyle change and reinforce the commitment to change Invite participants to come up with ideas to break up the sedentary time Review achievement (using the diary and Fitbit Flex 2 data) of the current goal Progress current goal(s) as able/required
Week 6: Setting additional goal	Review initial goal and discuss the progress of this goal (challenges) Evaluate the confidence about achieving the new goal (self-efficacy) Reinforce the health benefits of increased participation in PA and of breaking up sedentary time Congratulate any success and reflect on any difficulties Review achievement (using the diary and Fitbit flex 2 data) of the current goal Set a new smart goal as able/required
Week 7: Being rewarded	Identify the behaviour stage regarding physical activity Discuss the change (or not) that was achieved, as well as the benefits acquired with the new lifestyle Discuss positive reinforcement Review achievement (using the diary and Fitbit flex 2 data) of the current goal Set a final goal (number to steps)
Week 8: Goal balance	Final motivational interview (goal setting, benefits acquired and strategies to overcome barriers) Reinforce the importance of following through with these changes Establish a long-term goal to stay physically active

#### Participant Timeline

The schedule of enrollment, interventions, and assessments is outlined in Table 2. The recruitment of the study participants began in May 2022.

**Table 2 table2:** Content for the schedule of enrollment, interventions, and assessments.

		Time point				
		Enrollment	Allocation	Postallocation		
		–*t*_1_	0	Baseline	8 Weeks	16-Week follow-up
**Enrollment**						
	Eligibility screen	✓				
	Informed consent	✓				
	Allocation					
**Interventions:**						
	Behavioral intervention				✓	
**Assessments:**						
	Lung function			✓		
	PADL^a^ and sedentary behavior	✓			✓	✓
	Asthma Control	✓			✓	✓
	Asthma exacerbations			✓	✓	✓
	Quality of life			✓	✓	✓
	Anxiety and depression			✓	✓	✓
	Barriers to perform PADL			✓	✓	✓
	Behavioral stage for PADL			✓	✓	✓
	Anthropometric data			✓	✓	✓
	Body composition			✓	✓	✓

^a^PADL: physical activity in daily life.

### Outcome Measures

The primary outcome will be PADL (the number of steps per day) using an activity monitor (by actigraphy). Secondary outcomes will include clinical asthma control, quality of life, body composition and anthropometric data, anxiety and depression levels, asthma exacerbations, physical activity barriers, and behavioral stages for physical activity. This will be a single-blinded (outcome assessor) study in which assessments will be performed before, immediately after, and 16 weeks later.

#### Primary Outcome: PADL

PADL will be objectively assessed using an activity monitor (ActiGraph GT9X), a device that monitors frequency, intensity, and duration [27] in real time and is considered a sensitive and reliable method [28,29]. This triaxial monitor provides measurements of the amount and intensity of PADL and the monitoring of posture [27,30] through variations in acceleration. The “counts” obtained in a given period of time are linearly related to the intensity of the patient’s physical activity in this period [29]. Individuals will be instructed to use the accelerometer, attached to the hip using an elastic belt, for 7 consecutive days. All accelerometers will be initialized to collect data in 60 “epochs” on the 3 axes using ActiLife (version 6.9.5; ActiGraph) software. The following data will be later analyzed using the same software: the number of daily steps and the time spent in sedentary, light, moderate, and vigorous states of activity. Moderate to vigorous physical activity will also be evaluated. Sedentary behavior will be assessed using the same activity monitor.

#### Secondary Outcomes

##### Asthma Clinical Control

Clinical asthma control will be assessed using the ACQ, a reliable and validated tool [16,31] that comprises 7 questions [16]. Five questions are related to asthma symptoms (waking up at night, activity limitation, shortness of breath, and wheezing), 1 question is related to rescue medication (short-acting β_2_-agonist use), and 1 question is related to lung function (forced expiratory volume prebronchodilator, in percentage of predicted). The questions are scored on a 7-point scale ranging from 0 (no limitation) to 6 (maximum limitation), and the total score is the average of the 7 items, ranging from 0 (totally controlled) to 6 (severely uncontrolled). A cut-off value ≥1.5 indicates poorly controlled asthma, 0.75-1.5 indicates partially controlled asthma, and ≤0.75 indicates fully controlled asthma [16]. A change of at least 0.5 points in the ACQ score is considered clinically significant [32].

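### The ACQ is a seven-item mean that includes FEV1, but FEV1 is provided at baseline only, so the 8-week and 16-week ACQ scores have no current lung-function item

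*Protocol article*

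**What the plan says.** The Asthma Clinical Control section describes the ACQ as "a reliable and validated tool [16,31] that comprises 7 questions [16". Five items concern symptoms and one concerns rescue medication. The last is described thus: "1 question is related to lung function (forced expiratory volume prebronchodilator, in percentage of predicted". Each item is scored 0 to 6, and "the total score is the average of the 7 items". The same section states: "A change of at least 0.5 points in the ACQ score is considered clinically significant". The Sample Size Calculation section then adds: "Clinical improvement in the ACQ score (≥0.5) [3,32] will be considered a secondary outcome".

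Table 2 ticks asthma control at enrollment, 8 weeks and the 16-week follow-up. The row "Lung function" has one tick, at baseline. The Study Design section agrees: "Baseline lung function will be checked from the medical records". Its list of outcomes assessed over the study includes asthma control but not lung function.

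The only rule for absent data is in the Analysis of the Population section, which uses the patient's most recent assessment. The article names no shorter ACQ version and gives no rule for the FEV1 item specifically.

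**The concern.** The scoring rule needs an input at three visits that the schedule supplies once. This goes beyond detail left to a fuller document. The article fixes the item count, the averaging rule, the visit schedule and the source of lung function, and the four do not fit together. An analysis plan could replace the score, but it could not create FEV1 values that were never collected.

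At stake is the ACQ response of at least 0.5, the one secondary outcome that the sample-size section singles out. The repeated-measures comparison of ACQ at baseline, short term and medium term is also affected. Patients near the threshold can be classified differently depending on how the gap is filled, and the article does not say how it will be filled.

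**Working it through.** **The plan's own figure.** The only design calculation concerns steps, not the ACQ. A difference of 2500 with SD 2500, two-sided 5% and 80% power gives 16.71 per group on the t distribution, rounded up to 17, and 17/0.17 = 100. It reproduces, and nothing below touches it.

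**Inputs.** There are seven items, each scored 0 to 6, the score is their mean, and the threshold is 0.5 (Asthma Clinical Control; Sample Size Calculation). FEV1 is available at baseline only, from records (Table 2; Study Design). Let S be the sum of the six non-FEV1 items, m = S/6 their mean, and f the FEV1 item. The seven-item score is (S + f)/7 = (6m + f)/7.

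**Case A: chart value carried forward.** This is what the most-recent-assessment rule suggests if it is applied to a single item. Count improvement as positive.

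- Improvement with current FEV1: (improvement in S + improvement in f)/7.
- Improvement with f frozen: (improvement in S)/7.
- Error: (true change in f)/7, that is 1/7 = 0.143 per category.

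The error has no fixed direction:

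| True improvement in S | True change in f | Score with current FEV1 | Score with FEV1 frozen |
|---|---|---|---|
| 3 points | better by 1 | 4/7 = 0.571, response | 3/7 = 0.429, no response |
| 4 points | worse by 1 | 3/7 = 0.429, no response | 4/7 = 0.571, response |
| any | none | improvement in S/7 | the same |

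**Case B: seven items at entry, six at follow-up.** For a patient in whom nothing changes, the apparent improvement is (6m + f)/7 - m = (f - m)/7. The article gives no expected item values, so m is an assumption:

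- m = 1.5, f = 0: (0 - 1.5)/7 = -0.21.
- m = 1.5, f = 5: (5 - 1.5)/7 = +0.50, a recorded response with no change.
- m = 1.5, f = 6: (6 - 1.5)/7 = +0.64.
- Over m from 1.0 to 2.5 and f from 0 to 6, the range is (0 - 2.5)/7 = -0.36 to (6 - 1.0)/7 = +0.71.

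**Case C: the same six items at every visit.** The change is the change in m. Neither artefact arises, but this is not the score that the article defines.

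**The case against.** The strongest reply is that scheduling the ACQ implies collecting all its items. On that reading, the tick for asthma control at 8 and 16 weeks already includes a fresh FEV1, and the lung-function row is a separate baseline descriptor. Table 2 is also loosely drawn: it keeps an allocation row in a study where everyone receives the intervention, and it places the ACQ at enrollment but lung function in the later baseline column. It is true that the article nowhere says FEV1 will not be remeasured. But nothing in it says that it will be. Table 2, the chart source and the list of outcomes all point the other way. This reading therefore earns a place in the fix as an alternative, but it does not remove the conflict.

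A second objection concerns size, and it stands. A reader might infer that freezing FEV1 shrinks every ACQ change by 14% (1 - 6/7), or raises the bar by one third because 4 whole points are needed instead of 3. The documents do not support that. Any seven-item mean needs 7 x 0.5 = 3.5, hence 4 whole points, even with new spirometry at each visit. Those figures compare a seven-item with a six-item score. The proper comparator is the seven-item score with current FEV1, and against it the error is zero when the FEV1 category is unchanged and can run either way otherwise.

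It is also fair that the carry-forward rule points to Case A, and that no section proposes Case B. Case B is a risk left open, not a stated plan.

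**Conclusion.** The point holds as an internal conflict: the article defines a seven-item ACQ for three visits and provides the seventh item for one. With the chart value carried forward, each patient's ACQ change is in error by about 0.14 for every category by which the FEV1 item has truly moved, in either direction. No FEV1 change is given in the article, so the number of patients misclassified cannot be estimated, and neither systematic under-counting nor over-counting of responders can be claimed. If the item were dropped at follow-up only, the spurious change could reach the 0.5 threshold by itself, given the assumed six-item means above.

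The conclusion rests on reading Table 2 and the Study Design section as written, with no new spirometry after baseline. It is confined to ACQ change, the ACQ response and ACQ comparisons over time. The primary outcome, the 2500-step responder definition and the sample size are untouched. It should be corrected, but it does not threaten the study's main question.

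**What to change.** Compute ACQ change and the response of at least 0.5 from one item set collected at every visit, baseline included: the five symptom items plus rescue use. Keep the seven-item score for eligibility and baseline description only. State that the 0.5 threshold is assumed to apply to the six-item version, since the article attaches it to the seven-item score.

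Alternatively, if prebronchodilator FEV1 is in fact measured at each ACQ visit, correct Table 2 and the Study Design section to say so, and keep the seven-item score throughout.

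The six-item option needs no new data. Its cost is that the change is not directly comparable with published seven-item changes. In addition, 3 whole points (6 x 0.5) then suffice for a response, against 4 on the seven-item score when FEV1 is unchanged. The choice should therefore be fixed before the follow-up scores are analysed.
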